**Figure 2 F2:**
[figure not shown]
Flow diagram for; work package one to create FibroScan scripted feedback and work package two to create alcohol recovery videos stories. KLIFAD, Knowledge of LIver Fibrosis Affects Drinking; NEON, narrative experiences online; PPI, patient and public involvement; WP1, work package one.

We will organise separate participant and FibroScan operator focus groups to collect feedback on the prototype scripts. The participant focus group will allow us to investigate the key messages to be included in the script and feedback, as well as considering how best to present the FibroScan results (eg, graphically, in the text). The FibroScan operator focus group will specifically discuss implementation in clinical practice. In addition, to evaluate the stage of change that each participant has reached, a validated readiness to change model will be piloted.^22^

Following Krueger’s (1988) focus group guide, each focus group will include five to eight participants and will last for a maximum of 2 hours.^23^ Depending on the latest COVID-19 guidelines, the focus group will be either virtual or face-to-face. A topic guide will be used (SP-Focus Group Guide WP1 V.2.0). We aim to arrange two participant focus groups and one FibroScan operator focus group. The focus groups will be facilitated by two members of the research team. Examples of questions include: (a) If you were a participant in the trial, would the script make sense to you? (b) Are there any parts of the script that you do not understand, and if so, why? (c) What is the best way to present the results of the FibroScan (eg, graphically, in the text)?

Eligible participants (table 1) will be identified and recruited through multiple channels. For example, via existing patient forums at all three recruitment settings, the KLIFAD PPI group, by offering information to patients self-presenting to any of the trial treatment settings, snowball methods and via Black, Asian and minority ethnicity/Framework PPI groups. The focus group meeting will be recorded and transcribed verbatim either by automated software or an independent sponsor-approved transcriber. After the first participant focus group, the FibroScan script will be edited considering feedback and a second focus group will then be held to review iterated scripts. The final scripts will be sent via email to participants of focus groups for any final thoughts. We will then organise a FibroScan operator focus group of key alcohol workers working at any of the recruitment settings who are willing to give informed consent, to discuss any specific implementation issues.

**Table 1 T1:** KLIFAD trial eligibility criteria

Inclusion criteria	Exclusion criteria
Work package one	
A person age ≥18 years	Other primary substance misuse even where alcohol is a factor
Primary problem of alcohol misuse‡	Lacks capacity to confirm consent
Had FibroScan in past	
Work package two	
A person age ≥18 years	Lacks capacity to confirm consent
Primary problem of alcohol misuse	
Had FibroScan in past	
A person with lived experience of alcohol problems	
A person willing to consent to the recording and public use of their video recording	
Work package three: the randomisation phase	
A person age ≥18 years	Other primary substance misuse even where alcohol is a factor
Primary problem of alcohol misuse	Lacks capacity to confirm consent
	Referrals from driving offences and student referrals*
	Out of area clients at Edwin House†
	Participants unable to comply with trial procedures

*As these individuals are essentially not self-presenting, may have different motivation and have lower overall levels of alcohol use and so are substantially lower risk of having liver disease.

†In whom we cannot obtain follow-up data due to lack of follow-up availability.

‡Alcohol misuse was defined as, weekly alcohol intake ≥14 units, or an AUDIT score of ≥ 8, or key alcohol worker and/or physician diagnosis or referral from any other services with problem drinking.

AUDIT, Alcohol Use Disorder Identification Test; KLIFAD, Knowledge of LIver Fibrosis Affects Drinking.

After the focus groups, we will collect participant feedback on the change model (SP-Change Model Questionnaire (CMQ) V.1.0) to get an initial sense of the applicability of readiness to change following discussion about the scripts.

### Work package two (WP2)

WP2 aims to create a video library of ARVS from people with a history of alcohol misuse. These ARVS will be used in the feasibility RCT (WP3).

Receiving mental health recovery stories can provide benefits to some people experiencing mental health distress,^18 24 25^ and the effectiveness of mental health recovery stories as an intervention to increase quality of life has been examined in a clinical trial.^26^ However, equivalent evidence is not available for the impact of ARVS. So that we can explore the impact of stories of recovery from alcohol misuse, in WP2 we will develop a set of recovery stories from participants who have successfully overcome their alcohol misuse. These videos will be peer-reviewed by the KLIFAD PPI group which will include input from Nottingham University Hospitals NHS Trust (NUH) Black, Asian and minority Ethnic PPI group. Based on feedback, the videos will then be edited ready for use in the feasibility RCT (WP3). All edits will be agreed on with the story narrators.

For each narrator, we will follow their preference to create either:

A recovery story that starts with an open-ended question where narrators have the liberty to tell their story without interruption *or*A recovery story in which the participant is asked a set of standard questions.

Drinking history and last FibroScan reading will be included at the start of each video. Eligible participants (table 1) will be recruited through the channels used in WP1. Those who took part in WP1 will also be invited to take part in WP2. A purposive sample based on demographic and liver disease severity of six to nine individuals will be selected.^27^ We will arrange a meeting with the KLIFAD PPI group to discuss what makes a video impactful. The outline of WP2 is given in figure 2.

The ARVS will be recorded either at Nottingham Digestive Diseases Biomedical Research Centre (NDDC) Biomedical Research Centre Nottingham University Hospital, the University of Nottingham or the participant’s usual place of residence. Each video will be of 2–5 min duration. Videos will be titled based on FibroScan score (low-risk, medium and high-risk score). Videos will be subtitled and depending on the final video format, after the feedback, we envisage adding a photograph of the storyteller and a short-associated text on the title page with informed consent from the participant. The video stories will be brought together in a single-tablet computer-based package from which the participant will be able to choose their most preferred video after receiving a FibroScan score. Collaborative work between a clinician and patient can make a significant impact on the recovery process^28^ and hence in some videos, and with consent by narrators, we will include sections of a video narrated by a clinician the narrator has worked with.

All video stories recorded as part of the KLIFAD trial will have peer review by the trial team and KLIFAD/Black, Asian and ethnic minority PPI groups. The videos will be shown in the same format that they would be used in WP3.

### Work package 3 (WP3): feasibility RCT

A feasibility RCT of parallel groups (one-to-one) will compare usual care (assessment and entry into an alcohol reduction programme which does not include information on liver disease severity) to usual care plus feedback from the FibroScan and ARVS. The eligibility for WP3 is provided in table 1 and the attached flow chart (figure 3).

**Figure 3 F3:**
[figure not shown]
Flow diagram for work-package-three, the randomised control trial flow chart. Work package three is feasibility randomised control trial. AUDIT, Alcohol Use Disorder Identification Test; GCP, good clinical practice; KLIFAD, Knowledge of LIver Fibrosis Affects Drinking; RCT, randomised control trial; SADQ, Severity of Alcohol Dependence Questionnaire.

### Objectives

Bowen *et al*’s guide for feasibility studies was used to decide objectives.^29^

*Test*: the intervention (FibroScan plus feedback and ARVS) in a feasibility RCT.*Acceptability*: of feasibility RCT-related procedures and interventions among patients and healthcare workers.*Feasibility outcomes*: to establish recruitment rate, consent rate, dropout rate and completion rate for accurate sample size calculation for future large-scale RCT.*Refine*: the eligibility and randomisation criteria for a future large-scale RCT.*Implementation and practicality*: to assess the ability of community alcohol services to deliver the intervention, and training and support needs for community alcohol services keyworkers for delivering the intervention.*Adaptation*: of KLIFAD trial interventions, FibroScan feedback and ARVS format and access as per suggestions from participants and key alcohol workers*Limited efficacy*: to test limited efficacy of KLIFAD interventions

### Intervention group

Participants randomised to the intervention arm will receive a FibroScan, feedback on FibroScan results and watch ARVS immediately after. The ARVS will be made available should a participant wish to watch them later.

### Control group

Participants randomised to the control arm will continue with standard treatment (usual care) provided at the three treatment settings. The participants in this arm will be offered FibroScan at 6 months.

As part of standard treatment, the recruitment settings provide different types of interventions to participants in line with the National Drug Treatment Monitoring System Data set (NDTMS) and Public Health England (PHE) guidelines.^30^ Existing treatment programmes can run for up to 12 weeks.

For adult drug and alcohol services, there are three main categories of standard intervention (usual care) delivered by the NRN: (a) Psychological: which includes motivational interventions, family and social network interventions and cognitive and behavioural-based relapse prevention interventions (substance misuse specific). (b) Recovery support: which includes 12-step work and counselling.

(c) Pharmacological: which involves prescribing medication for drug and/or alcohol relapse prevention support. For example, naltrexone, acamprosate, disulfiram as part of alcohol or opioid relapse prevention therapy and Chlordiazepoxide for acute alcohol withdrawal.

Specific treatment programmes are started after an initial assessment and based on the participant’s needs. The duration of contact with services varies, most participants stay with services for 12 weeks, some get discharged early and a few stay longer than 6 months.

### Methods

#### Sample size

As this is a feasibility trial, a formal sample size calculation for between-group comparisons of a primary outcome is not appropriate. Researchers have previously recommended sample sizes between 24 and 50 to satisfactorily achieve feasibility outcomes.^31–33^

After discussion with community alcohol services data manager and considering variation in number of patients presenting per week, we aim to approach 40 eligible participants per month. Assuming a 50% consent rate, we anticipate randomising 20 participants per month (10 per month per arm) for a recruitment period of 6 months. With an estimated sample size of 120, we will be able to calculate a dropout rate of 80% within a 95% CI of±7.1%. Assuming a non-differential follow-rate of 80%, this target sample size should provide follow-up outcome data on a minimum of 48 participants in each of the two arms.

#### Randomisation

The participants will be individually allocated on a one-to-one ratio using minimisation with a probabilistic element. The minimisation variables will be age, gender, ethnicity and severity of alcohol misuse based on the Severity of Alcohol Dependence Questionnaire (SADQ) score. To minimise selection bias, the randomisation will be externally performed by a data manager from NRN.

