## Methods and analysis

KLIFAD is a parallel design feasibility RCT. The trial will be conducted in a single centre in the UK, carried out at three community alcohol services in Nottingham (the Wellbeing Hub, Edwin House and the Primary Care Alcohol Clinic run by the NRN) hosted by Framework and NRN and working in partnership with Nottinghamshire NHS Foundation Trust.

The KLIFAD trial consists of three work packages (WP) (figure 1).

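### Minimisation omits treatment setting although the trial runs through three services: a minor, cheap improvement to the allocation

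*Protocol article*

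**What the plan says.** Under Randomisation, the protocol article says that participants are "individually allocated on a one-to-one ratio using minimisation with a probabilistic element", and then lists the factors: "The minimisation variables will be age, gender, ethnicity and severity of alcohol misuse based on the Severity of Alcohol Dependence Questionnaire (SADQ) score". Setting is not listed.

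Under Methods and analysis, the trial is described as single-centre but "carried out at three community alcohol services in Nottingham". Under Schedule of visits, the baseline visit, with consent and randomisation, falls on the day a participant starts standard treatment at one of the settings, so setting is known before allocation. The 3-month visit involves no research activity, and its data come from the three settings' routine records.

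On usual care, the Control group section says "the recruitment settings provide different types of interventions to participants". It then describes three categories of care delivered by one network, and adds: "Specific treatment programmes are started after an initial assessment and based on the participant’s needs".

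The only setting-specific remark about follow-up is in Table 1. Out-of-area clients at Edwin House are excluded from the randomised phase, with the footnote "In whom we cannot obtain follow-up data due to lack of follow-up availability".

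The statistical section makes the analysis descriptive, states that the trial is not powered for a between-arm comparison, and plans to present feasibility results by categories of age, gender, ethnicity and severity of alcohol misuse. Limited efficacy is nevertheless one of the objectives, as is refining the randomisation criteria for the later trial.

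**The concern.** Where participants come through several services, the service is a natural balancing factor. It is recorded before allocation, and it can stand in for differences in case mix, in the care received in both arms and in attendance. Here the 3-month data depend on attendance and recording at each service, so completeness at that visit could vary by setting.

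If setting is not balanced, the two arms can end up with different mixes of services by chance. Retention by arm, the sample size section's assumption of equal follow-up in the arms, and the limited-efficacy comparison would then partly reflect that mix. With 120 participants there is little room to separate the two afterwards. The trial also aims to prepare a larger national trial, in which allocation across many services will have to work, so this is a natural place to try it.

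**Working it through.** **1. The plan's own figures.** From the Sample size section: 40 approached per month × 50% consent × 6 months = 120, or 60 per arm. Followed up: 60 × 0.80 = 48 per arm. The 95% half-width at 80% with n = 120 is 1.96 × √(0.8 × 0.2 / 120) = 7.16 points by the Wald formula and 7.11 by Wilson, so the stated ±7.1 is reproduced by Wilson. These figures refer to total numbers or to the pooled sample and do not depend on setting.

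**2. Chance imbalance in setting, fixed setting sizes.** The article does not give the number expected from each service, so two splits are assumed: 40/40/40 and 60/40/20. If allocation is 60:60 and unrelated to setting, a setting of size n contributes x participants to one arm and n − x to the other. Its share differs between the arms by |2x − n| / 60. Each allocation (x₁, x₂, x₃) with x₁ + x₂ + x₃ = 60 has probability C(n₁, x₁) C(n₂, x₂) C(n₃, x₃) / C(120, 60). Summing over allocations in which at least one setting reaches the threshold gives:

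| Largest difference in any setting's share | 40/40/40 | 60/40/20 |
|---|---|---|
| at least 15 points | 18.8% | 15.9% |
| at least 20 points | 8.2% | 6.9% |

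**3. Do the four listed factors balance setting indirectly?** Minimisation was simulated (1,500 runs per scheme) for 120 people. The assumptions, none of them in the article, were a probability of 0.8 for the favoured arm, two or three levels per factor, factors unrelated to setting, and setting proportions of 33/33/33, 50/30/20 or 60/30/10%. Setting sizes were drawn at random, so the results differ a little from step 2.

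| Largest difference in any setting's share | Four factors | Four factors plus setting |
|---|---|---|
| median | 8 to 10 points | 3 points |
| chance of at least 10 points | 41 to 51% | 0.6 to 1.5% |
| chance of at least 15 points | 16 to 20% | about 0% |

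The four-factor results are close to those for a plain random 60:60 split (16 to 22% for at least 15 points). If the listed factors were correlated with setting, they would give some indirect balance.

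**4. What an imbalance would do to retention by arm.** Suppose follow-up at one setting is 25 points below that at the other two (an assumption). A 15-point difference in that setting's share then moves the arm difference in retention by 0.15 × 0.25 = 0.0375, or about 4 points. With gaps of 10 to 30 points the shift is 0.15 × 0.10 = 1.5 to 0.15 × 0.30 = 4.5 points. The standard error of the arm difference in retention is √(2 × 0.8 × 0.2 / 60) = 7.3 points.

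**5. How often that shift would arise.** The 16 to 19% in step 2 is the chance that any of the three settings is imbalanced. The shift in step 4 needs the imbalance to fall on the low-follow-up setting. For one named setting, the exact hypergeometric chance of a difference of at least 15 points is 2.6% if it has 20 people, 8.1% if 40 and 10.0% if 60, in either direction.

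**The case against.** A reader might infer something stronger: that the three settings give different usual care and that follow-up differs between them. The documents support neither as fact.

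- **Follow-up.** The Edwin House footnote is attached to an exclusion, so that group is never randomised. The Data collection section says all three services record the same outcomes, and the 6-month contact is made by the research team.
- **Usual care.** The sentence about different types of intervention can mean a range of options offered across the settings just as well as differences between them. No service is tied to a particular type of care, and the text makes participant need, not setting, decide the programme.

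These points stand. The supportable statement is that case mix, care and attendance may differ by setting.

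The other side can also say that chance imbalance under random allocation is not bias, that the analysis is descriptive and unpowered, that the pooled feasibility rates do not depend on balance by setting, and that the choice of minimisation factors is a judgement. All of this is right, and it makes the point minor. It does not remove it. By-arm comparisons are still planned, setting is neither balanced nor among the variables by which results will be presented, and the omission is a choice that the article itself states. That randomisation criteria are to be refined for the later trial is, if anything, a reason to try setting as a factor now.

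**Conclusion.** The point holds as a minor design improvement. Setting is known at allocation and is left out of the minimisation. At 60 per arm, some setting's share would differ between the arms by at least 15 points with a chance of about 19% (40/40/40) or 16% (60/40/20), and the four listed factors do little to prevent it if they are unrelated to setting.

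The consequence is limited to retention by arm and the limited-efficacy comparison. Even with an assumed 25-point follow-up gap at the imbalanced setting, the shift of about 4 points is roughly half the 7.3-point standard error (3.75 / 7.3 ≈ 0.5). Recruitment, consent and overall retention are unaffected, as are the sample size of 120 and the ±7.1 precision.

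The setting sizes, the follow-up gap and the details of the minimisation scheme are assumptions. The omission should not be described as a source of bias or as a fault in the main feasibility results.

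**What to change.** Add treatment setting, with three levels, to the minimisation variables in the Randomisation section, and keep the probabilistic element. If the sponsor prefers to leave setting out, a sentence giving the reason would do.

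The cost is one line in the protocol and one field in the minimisation program, with no change to sample size or precision. The downside is that allocation becomes slightly easier to guess within a setting, which the probabilistic element limits.

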#### Schedule of visits

##### Baseline

The baseline visit will be on the day when the participant starts standard treatment at any recruitment setting. At this visit, written informed consent will be given by participants and participants will be randomised to the intervention or control group. Participants in both arms will have an initial detailed assessment (SP-NRN assessment form online supplemental material 2) as part of their standard care. This includes the collection of baseline demographic and clinical data (eg, age, gender, ethnicity). Participants randomised to the control arm will continue with usual care, while participants randomised to the intervention arm will have the usual care and FibroScan followed by standardised script feedback with ARVS watched immediately after the FibroScan result.

10.1136/bmjopen-2021-054954.supp2Supplementary data

##### Three months

This visit will be part of usual care, no research specific activity will be carried out. The research data will be extracted from routinely collected data from three treatment settings.

##### Six months

This will be a telephone consultation or in-person appointment by the research team. Participants in the control arm will be offered a FibroScan after completion of outcomes. The 6-month follow-up is specifically to cover those who were lost to follow-up at NRN from the treatment programme.

A detailed schedule of the visits is given in table 2.

**Table 2 T2:** Work-package-three (feasibility RCT) schedule of visits and variables for data

Trial activity	Baseline visit	3* months	6† months
Control group			
Date and time	Yes	Yes	Yes
Baseline consent	Yes	–	–
FibroScan+feedback	–	–	Yes
Watching video stories	–	–	Yes
Qualitative interview	–	–	Yes
Demographics	Yes	–	–
AUDIT score	Yes	Yes	Yes
SADQ score	Yes	Yes	Yes
Self-reported alcohol intake‡	Yes	Yes	Yes
Breath alcohol test	Yes	Yes	Yes
Substance misuse other than alcohol	Yes	Yes	Yes
Data on feasibility outcomes	Yes	Yes	Yes
Intervention group			
Date and time	Yes	Yes	Yes
Baseline consent	Yes	–	–
FibroScan+feedback	Yes	–	–
Watching video stories	Yes	–	–
Qualitative interview	–	–	Yes
Demographics	Yes	–	–
AUDIT score	Yes	Yes	Yes
SADQ score	Yes	Yes	Yes
Self-reported alcohol intake	Yes	Yes	Yes
Breath alcohol test	Yes	Yes	Yes
Substance misuse other than alcohol	Yes	Yes	Yes
Data on feasibility outcomes	Yes	Yes	Yes

*3-months visit: this will be routine visit no trial-specific procedure will be carried out.

†6-months visit: will be a telephone consultation and/or if possible/required in person. The participant in the control group will be offered a FibroScan at 6 months if they attend it will be in-person appointment.

‡Self-reported alcohol intake in gram and units per week.

AUDIT, Alcohol Use Disorder Identification Test; RCT, randomised controlled trial; SADQ, Severity of Alcohol Dependence Questionnaire.

